## Abstract

**Background:**

This protocol describes a study designed to test the implementability and proximal effects of a transdiagnostic mental health intervention for adolescents in school health services. The study is driven by the urgent need to address the rising mental health challenges among adolescents, exacerbated by the COVID-19 pandemic. Leveraging implementation science and evidence-informed intervention elements, this co-designed intervention focuses on emotion regulation (ER) as a central target for usable prevention and support.

**Methods:**

The study employs a mixed-methods approach, integrating intensive longitudinal experience sampling (daily measures for 13 weeks), a micro trial, pre-, post-, and follow-up measures, audio recordings, and qualitative interviews to triangulate data from school nurses and adolescent participants. The research questions span the domains of intervention implementability, barriers and facilitators to implementation, proximal outcomes for adolescents’ emotion regulation, the mechanisms driving the intervention’s proximal effects, and response burden in experience sampling. The study aims to recruit a minimum of 25 health nurses and 46 adolescents.

**Discussion:**

The study is novel in using mixed methods from multiple theoretical paradigms to examine ER as a dynamic process and transdiagnostic target outcome for promoting mental health and preventing disorders. Through daily diary and ecological momentary assessments, the study explores the intricacies of ER in real-life settings. Coupling the experience sampling with highly detailed fidelity measurement, we will observe adolescents’ day-to-day responses to intervention elements and how they affect emotion regulation. The integrated micro-trial also addresses concerns about response burden in experience sampling to optimize data collection strategies for future studies.

The findings from this study can increase our understanding of ER as a mental health process, and contribute to the development of scalable, efficient, and context-appropriate mental health interventions in school nursing.

**Trial registration:**

The ISRCTN-registry: ISRCTN14932526, registration date 04/04/2023.

**Supplementary Information:**

The online version contains supplementary material available at 10.1186/s12913-025-12661-5.

## Introduction

Mental disorders exert substantial adverse effects on public health, human development, well-being, and the global economy [1]. The consequences encompass reduced quality of life, poor physical health, premature mortality, school dropout, unemployment, criminal behavior, and other detrimental outcomes [2]. Up to 86% of individuals will encounter mental disorders during their lifetime, with a significant proportion meeting the criteria for multiple diagnoses [3]. Mental health issues predominantly emerge during adolescence, with the onset of more than half of all mental disorders occurring by age 14 [4].

A wealth of scientific literature outlines interventions and treatments that hold promise for preventing, treating, and reducing societal mental health burdens [5, 6]. However, widespread implementation failures across health systems globally hinder access to quality prevention and care [1]. For instance, only around 10% of individuals with anxiety disorders worldwide receive adequate care [7], and the best available care delivered to an entire population in need will reduce only around 28% of the disease burden [8]. Also, a recent review of over a thousand attempts to implement evidence-informed programs found that more than 85% either discontinued or never achieved quality delivery [9].

Despite such severe challenges in scaling effective mental il prevention and treatment to reach populations in need, evidence-informed interventions evidently have elements and features that can effectively address mental health issues [10–12]. The critical hurdle may be finding more context-appropriate, efficient, and scalable models and systems for implementing and supporting evidence-informed mental illness prevention in practice. Consequently, collaboratively tailored, transdiagnostic, modular, and process-focused interventions are advocated as potential advancements [13–17].

This study explores novel approaches to develop and implement mental illness prevention and mental health promotion for adolescents. The study leverages implementation science and common elements of effective mental health interventions for adolescents to collaboratively design effective transdiagnostic and context-appropriate mental health practices to be widely delivered in school health services.

## Background

### The need for mental health prevention and support for adolescents

Adolescence is characterized by profound biological, neurobiological, social, emotional, and cognitive changes. These changes make adolescents particularly vulnerable to develop mental health issues [3, 13]. Worldwide, it has been estimated that 13% of adolescents meet the criteria for a mental disorder [18]. In Norway, 15–20% of children and adolescents grapple with significant mental health challenges, with 13% meeting the criteria for a psychiatric diagnosis [19]. Early age elevations in symptoms such as depression, anxiety, and behavioral problems predict unfavorable outcomes, including mental disorders, dropout, substance abuse, marginalization, unemployment, and social conflicts [20]. The last decade has seen a steady increase in mental health challenges among Norwegian adolescents, especially among females [21]. Recent reports indicate that this increase was exacerbated by the Covid-19 pandemic for adolescents already at risk [22, 23]. There is an acute need for mental health support for adolescents to improve wellbeing and prevent societal strains and costs.

Norwegian municipalities provide frontline services targeting the health and well-being of adolescents, and the school health service is a mandatory part of these services. The school health services are located at schools, are free of cost for all students, and health promotion and illness prevention are core aims. School health service providers are well-positioned to provide early-stage mental health support to a large portion of adolescents. However, there is a lack of effective interventions that appropriately fit their services and needs. While interventions developed to prevent and mitigate mental health issues show the potential to reduce the risk of future mental disorders [6, 24], they encounter several limitations when they are introduced into frontline services [9, 25]. Primarily, these interventions focus on singular disorders or problems, disregarding the fact that most adolescents in need of mental health support grapple with an array of issues and comorbidities. Moreover, practitioners are compelled to learn and use as many interventions as there are problems. This is unfeasible considering the total complexity, cost, and time requirements for their implementation and maintenance. Further, the transferability and usability of an intervention may be limited if it has been developed and tested in contexts divergent from Norwegian frontline services.

### Emotion regulation as an intervention target

Emotional concerns constitute the primary reason for adolescents to seek frontline mental health services in Norway [26], emphasizing the need for emotion-focused care and support. This help-seeking may also present an opportunity for wide-reaching mental illness prevention through training and supporting adolescents in emotion regulation skills. Emotion regulation (ER) encompasses the management of one’s own and other’s emotions in response to contextual demands, impacting emotional intensity, duration, and expression [27]. To regulate emotions, individuals employ both adaptive (e.g., acceptance) and maladaptive (e.g., avoidance) strategies. Emotional dysregulation (i.e., inability to regulate emotions or excessive use of maladaptive strategies) is linked to diverse mental health problems such as anxiety, depression, eating disorders, conduct disorder, attention-deficit/hyperactivity disorder, and psychotic disorders [28]. ER is perceived as a transdiagnostic process because maladaptive ER strategies span diagnoses and contribute to general psychopathology development and maintenance [13, 29].

The propensity to self-regulate emotions changes with brain maturation during late childhood and adolescence [30]. Coinciding with heightened brain plasticity, puberty, and an increase in social stressors and demands, adolescence is thus a critical period for the neurodevelopment of adaptive ER strategies rather than maladaptive ones associated with psychopathology [13]. There is evidence for an increase in the use of maladaptive strategies in adolescence compared to earlier or later ages [31]. Subsequently, ER is a suitable target for interventions targeting adolescents’ mental health because ER is a malleable processing skill that can be trained. A recent meta-analysis assessing the effectiveness of interventions targeting ER for adolescents found moderate effects on decreasing emotion dysregulation, small effects on improving emotion regulation, with subsequent decrease in emotion dysregulation being associated with improvements in mental health [32]. There is, however, limited evidence about the elements and mechanisms of the interventions (i.e., discrete practices, processes, or principles) and how and for whom these elements can and cannot drive improvements in ER skills [32]. A systematic review by Helland et al. [11] and a currently unpublished sytematic review conducted by the project group identified a total of 16 commonly effective elements of current interventions targeting ER for adolescents that can be tailored for testing in school health services. The current intervention, named *Kort* (Norwegian for *Brief)*, draws on these evidence-informed intervention elements focused on improving ER.

### Co-design for implementability in natural practice

The proliferation of implementation science has revealed that most efforts to implement evidence-informed interventions in practice fail [1, 9]. Implementation researchers have pointed to a disconnect between the study conditions under which interventions are found effective in research and what is feasible and appropriate in natural practice conditions [14]. The discrepancy between the resources and infrastructure available in research studies compared to everyday frontline services [14] is a significant contributor to why few evidence-informed interventions are implemented and sustained as intended [25]. A remedy to this discrepancy is to ensure that the intervention is tailored to be *implementable* within the constraints and resources of its intended everyday end destination. In addition, the implementation strategies need to be tailored to address local contextual determinants and needs. Implementability is a quality that encompasses how usable, appealing, appropriate, and fitting the content of the intervention is to those who engage with it. Further, it encompasses how the intervention content is designed, shaped, or packaged in ways that facilitate or inhibit implementation and sustainment in a given context [33].

While intervention effectiveness can indicate the degree to which the intervention can potentially prevent and/or alleviate mental health challenges, implementability can be a proxy for the likelihood that the intervention can reach those in need. However, effective and contextually appropriate implementation strategies are necessary to succeed. In their study of 1287 implementations of evidence-informed interventions, Alley et al. [9] found that nearly all implementations fail if they do not include a rigorous pre-implementation phase with activities such as collaboratively tailoring the intervention and implementation strategies and working to solve barriers to implementation. To this end, we have collaboratively designed the Kort intervention with school nurses, adolescents, and intervention specialists. We have combined implementation science with co-design methods and principles tailored to achieve implementability within the natural practice of school health services [33]. To tailor contextually appropriate implementation strategies (e.g., training, supervision, leadership support, relational strategies, nudges), we conducted a pre-implementation study to address local implementation barriers and facilitators.

### Studying emotion regulation as a dynamic process

ER has been identified as a central mechanism of change in mediation studies investigating the effect of interventions on mental health [34]. The link between ER and mental health difficulties has primarily been investigated considering ER as a stable trait. Yet, the selection of ER strategies is context-dependent [35], and therefore varies in adolescents’ day-to-day lives [36]. Research has also shown modest correlations between ER measured as a trait compared to momentary assessments of ER [37, 38]. Regarding intervention research, the sole use of pre- and post-assessments of ER limits researchers from determining when, how, and in response to which elements change occurs [39]. With daily measurements of ER, we can investigate ER as a dynamic process in relation to the intervention and the mechanisms that lead to improved mental health and well-being. Similarly, we can investigate whether and how any unintended negative effects caused by the intervention or participation emerge and for whom. Studying ER as a process is complex, given that what drives changes may vary widely (see [40] for an overview). Several different mechanisms have been hypothesized to be involved with positive outcomes, for example, increasing the repertoire of ER strategies, decreasing the frequency of use of typical maladaptive strategies, and flexibly using different ER strategies [40]. By coupling detailed intervention fidelity measures with daily ER measurements, we can explore how specific facets of intervention fidelity (e.g., component adherence, competence, alliance) are associated with ER processes and mechanisms.

The use of experience sampling allows for measuring ER in real-life settings by minimizing recall bias and increasing the likelihood of accurate reports [41]. However, the literature is not clear about the effects of frequent data collection on adolescent motivation and engagement. A meta-analysis of ecological momentary studies showed that financial incentives were the only significant predictor of compliance, whereas the design, sample characteristics, or number of assessments had little effect [42]. One study collected data daily from adolescents for 100 days and reported a response rate of 86% [43]. In the current study we will investigate the potential burden of frequent data sampling by asking half of the sample to answer daily questions and the other half to answer additional questions three times a day in bursts. Quantitative and qualitative information about the adolescents’ experiences with the data collection will help optimize an experience sampling system, balancing data quality with response burden to be used in future studies.

In sum, there is a need for novel scalable interventions targeting transdiagnostic processes (i.e., ER) within the adolescent population, with a focus on effectiveness, efficiency, and implementability in Norwegian frontline mental health services. Therefore, we have - together with researchers, practitioners, adolescents, and other stakeholders - co-designed an evidence-informed intervention targeting ER for wide delivery in school health services.

### The current study

This study aims to test the Kort intervention in the natural practice of school health services. The study employs intensive longitudinal methods and is a hybrid type 2 study because it focuses both on the interventions’ implementability in school health services and its proximal effectiveness on emotion regulation strategies for adolescents. Estimating proximal effectiveness and implementability will indicate the intervention’s causal and contextual potential. In combination, these estimates will indicate the intervention’s potential for impact on a larger scale. We will triangulate detailed measures of intervention fidelity, intensive experience sampling methods, audio recordings, and qualitative interview data from school nurses and adolescent participants. This will enable us to investigate proximal mechanisms and processes of change in ER in response to intervention elements. The study will address the following research questions:1.1. How feasible, acceptable, appropriate, and usable (i.e., implementable) is Kort in school health services?1.2. How can the implementability of Kort be improved?2.1. What are the barriers and facilitators to, and potential consequences of, the implementation of mental health interventions in school health services?2.2. How can implementation strategies be appropriately designed to address barriers and facilitators and avoid negative consequences?3.1. How does Kort affect proximal outcomes for adolescents’ emotion regulation?3.2. How can the effectiveness of Kort be improved?3.3. Through which mechanisms does the Kort intervention affect adolescents?3.4. For whom and in what circumstances does Kort improve emotion regulation, and when and for whom does it not?4. What are adolescents’ and school nurses’ experiences with implementation, the Kort intervention, and its value?5. How does the combination of daily diary and ecological momentary assessments affect response rates?

## Methods

### Setting

The study is conducted in school health services serving Norwegian lower (grades 8–10) and upper secondary schools (grades 11–13). The school health service work on directions and guidelines from the Norwegian Directorate of Health, and their main mandate is to promote health and well-being and prevent disease. All 8th graders have a mandatory consultation with school nurses to have a physical checkup and talk about health literacy and general coping. School nurses work on individual, group, and universal levels and offer a range of services, from individual consultations to classroom health literacy teaching and vaccination. Most school health services have 1–4 school nurses serving 1–5 schools, and the school nurses are typically located at the schools. Adolescents can visit the school nurses whenever they need to during school hours. They typically come to talk about peer and family issues, health-related questions and concerns, sex and contraceptives, and bullying. The last decade has seen a marked increase in adolescents visiting school nurses expressing trouble coping with emotions and stress [26]. However, school nurses have limited or no formal training in mental health prevention and intervention.

### Participants and criteria

We aim to recruit 25 school nurses from school health services serving either lower or upper secondary schools, or both. The school health services will be located in both rural and urban areas in the southeastern region of Norway. We aim to recruit a minimum of 46 adolescents in lower secondary school (age 12–16) and upper (age 16–18). Adolescents aged 12–15 will need informed consent from primary caregivers to participate. Adolescents aged 16 or older will provide informed consent on their own behalf. Consent forms are available in Supplementary file 3.

#### Inclusion and exclusion

School nurses will invite adolescents who approach them due to sub-clinical mental health-related concerns to participate in the Kort study. We operationalize sub-clinical mental health concerns as expressions or signs of mild to moderate mental health issues and challenges. Exclusion criteria and discontinuation are concerns about clinical mental health issues requiring referral to specialist mental health services. School nurses consider such concerns in the same manner as they normally do, in line with their mandate. Other exclusion criteria are known autism and severe developmental disorders. Adolescents with attention-deficit/hyperactivity disorder will be invited to participate. Adolescents with mental health issues at or above a clinical level will be referred to appropriate services following regular routines in the school health service.

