## Design

To assess the implementability and proximal effects of the Kort intervention, we will use a mixed-methods combination including an intensive longitudinal time series and a quasi-experimental pre-post design. Qualitative data will be collected using individual interviews with adolescents, focus group interviews with school nurses, and audio recordings of consultations between school nurses and adolescents. Quantitative data will be collected using pre- and post-questionnaires and experience sampling measures (daily diaries and ecological momentary assessments; EMA).

To test how the combination of daily diaries and EMA will affect response rates we will conduct a two-arm micro trial within the study where adolescents are randomized to either daily diary sampling only (one measurement per day), or daily diary and EMA (between one and four measurements per day).

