### Data collection and outcomes

Table 3 depicts outcomes, instruments, data collection methods, informants, and time points for all measures used in the study. The time points correspond to two weeks prior to the start of the intervention (T1), once the adolescent completes the intervention (dynamic post measure, T2), 11 weeks after the intervention begins (T3), and again 11 weeks after T3 (T4) to serve as pre- post- and follow up assessments, respectively. The experience sampling measures will have a two-week baseline assessment between T1 and the intervention start.

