**Fig. 2 Fig2:**
[figure not shown]
Experience sampling in the experimental groups. Note. The dynamic T2 will be sent when school nurse prompts in the fidelity measure that they have completed the intervention. This can be done up until T4. T3 is sent when the experience sampling ends, T4 is sent 11 weeks after T3

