### Data analysis

#### Quantitative analyses

We will be analyzing the data from the adolescents descriptively and at the individual level using appropriate analyses for single-case experimental designs (e.g., autoregressive integrating moving average analyses; ARIMA) and at the group-level using appropriate intensive longitudinal analyses (e.g.,multilevel modeling, dynamic structural equation modelling; DSEM), accounting for gender and age. Analyses will be informed by the conceptual model to investigate associations between the elements the adolescents are given and change in specific emotion regulation strategies. We will use repeated measures ANOVA to compare group pre-, post-, and follow-up means on adolescents’ emotion regulation and mental health outcomes, and mixed models for testing multilevel associations between nurses’ intervention fidelity and adolescents’ outcomes. Data about implementation determinants will be analyzed descriptively. We will assess the extent of missingness, and explore the possible reasons for missing (e.g., missing not at random or missing at random). Missingness in experience sampling data will be handled by implementing full information maximum likelihood. Missingness in pre-, post-, and follow-up data will be handled using multiple imputation. The percentage of compliance of intensive longitudinal data will also be assessed.

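### Adolescents discontinued for clinical concern get no T2 as the trigger is written, so the uncontrolled T1–T2 comparison loses participants for a reason closely tied to the outcome

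*Protocol article*

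**What the plan says.** Under Inclusion and exclusion, the protocol article gives one criterion two uses, entry and stopping: "Exclusion criteria and discontinuation are concerns about clinical mental health issues requiring referral to specialist mental health services". The judgement is the nurse's and has no scale or cut-off: "School nurses consider such concerns in the same manner as they normally do, in line with their mandate".

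The note to Fig. 2 gives the T2 trigger: "The dynamic T2 will be sent when school nurse prompts in the fidelity measure that they have completed the intervention". Data collection and outcomes agrees, placing the assessments at "once the adolescent completes the intervention (dynamic post measure, T2), 11 weeks after the intervention begins (T3"). T3 and T4 follow the calendar: "T3 is sent when the experience sampling ends, T4 is sent 11 weeks after T3".

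DERS-SF, BFS and SWEMWBS are the effectiveness measures at T1, T2, T3 and T4 (Effectiveness of the intervention). The design is described as "an intensive longitudinal time series and a quasi-experimental pre-post design". The only randomised contrast is between two sampling frequencies, so no group goes without Kort.

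Under Quantitative analyses, group means are compared by repeated measures ANOVA, and "Missingness in pre-, post-, and follow-up data will be handled using multiple imputation". Experience sampling data are handled by full information maximum likelihood (FIML). The same paragraph says the reasons for missingness will be explored, including missing not at random, but names no analysis for that case.

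**The concern.** The discontinuation rule and the T2 trigger are each reasonable alone, but together they select on the outcome. A nurse who becomes concerned that problems have reached clinical level is reacting to something close to what BFS, SWEMWBS and DERS-SF measure. The adolescent who prompts that concern does not complete Kort, so the completion prompt is not given and T2 is not sent.

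In a two-arm trial a similar loss in the control arm would offset some of the distortion. Here the estimate is a within-group change, so a loss driven by deterioration passes straight into the mean and makes Kort look better. Imputation does not repair this if the reason for the loss is a worsening seen by the nurse but absent from the data used to impute.

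It also bears on the stated aim of studying "whether and how any unintended negative effects caused by the intervention or participation emerge and for whom". The adolescents most informative for that aim are the ones who would lack the dynamic post measure.

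**Working it through.** **Plan's own figure.** The only figure on loss is up to 15% dropout, with 46 recruited to keep 40. 40 × 1.15 = 46 reproduces it; 46 × 0.85 = 39.1, close to 40. The article gives no rate of discontinuation for clinical concern. I therefore assume 5%, 10% and 15% (46 × 0.05 = 2.3 to 46 × 0.15 = 6.9 adolescents). Since 15% is dropout for any reason, it is an upper bound.

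**Illustration 1: questionnaire change, T1 to T2.** Assumed: T1 (X) and T2 (Y) are standard normal, higher is worse, true mean change is zero and correlation ρ = 0.6. The worst share p on Y is lost. Let z be the (1 − p) normal quantile, m = φ(z)/(1 − p), and v = 1 − zm − m² the variance of Y among those kept.

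- Completers: bias = −(1 − ρ)m.
- Imputation from T1 alone: the slope in completers is b = ρv/(ρ²v + 1 − ρ²), and bias = −m(1 − bρ).

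| p | m | v | b | Completers | Imputed from T1 |
|---|---|---|---|---|---|
| 5% | 0.109 | 0.810 | 0.522 | −0.4 × 0.109 = −0.043 | −0.109 × (1 − 0.313) = −0.075 |
| 10% | 0.195 | 0.712 | 0.477 | −0.078 | −0.139 |
| 15% | 0.274 | 0.641 | 0.441 | −0.110 | −0.274 × (1 − 0.265) = −0.202 |

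Negative means apparent improvement. If nurse judgement shares only half its variance with Y, the completer bias is multiplied by √0.5 = 0.707, giving −0.031, −0.055 and −0.078. The same derivation for imputation gives −0.051, −0.093 and −0.133.

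Across both cases the range is 0.03–0.11 SD in completers and 0.05–0.20 SD after imputation from T1. Imputing from T1 alone increases the bias here. It corrects for the lost adolescents' higher T1 scores but not for their worse T2.

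**If T3 is still collected and used to impute T2.** With assumed correlations of 0.6 (T1–T2 and T1–T3) and 0.7 (T2–T3), and loss exactly on Y, simulation gives 0.055, 0.106 and 0.156 SD. Continuing T3 helps but does not replace T2.

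**If selection is on T1 instead.** By symmetry the completer bias is +(1 − ρ)m, an apparent worsening of 0.04–0.11 SD. Imputation from T1 is then valid.

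**Illustration 2: the protocol's own variances** (intercept 0.7, slope 0.3, residual 0.3; 46 adolescents; 10 points before and after; true change zero). Simulated spurious improvement at 5%, 10% and 15% loss:

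| Who is lost | Completers | Imputed from baseline |
|---|---|---|
| Worst change | 0.05, 0.11, 0.15 | 0.05, 0.11, 0.15 |
| Worst later level | 0.03, 0.07, 0.08 | 0.04, 0.09, 0.12 |
| Later level, noisily judged | 0.02, 0.04, 0.06 | 0.02, 0.05, 0.07 |

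When five diary points taken after the change but before discontinuation enter the imputation model (loss by worst later level), the bias falls to about 0.01–0.02. That is a favourable case, because the simulated diary measures the same quantity as the outcome being imputed.

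**The case against.** Several counter-arguments have force.

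- **Only T2 is lost by the trigger.** A reader might infer that adolescents who worsen leave the whole pre-post analysis. The documents do not support that. T3 and T4 go out by calendar, and the daily diary is given every evening during the data collection period. The article does not say whether discontinuation ends any of these, and the full protocol and supplementary files may. This stands, and it limits the point to T2 plus a request for clarification.
- **The plan does not state a missing-at-random assumption.** It says it will explore missing-not-at-random reasons. This stands in part: the possibility is recognised, but the methods named rely on missing at random in standard form and nothing is named to follow the exploration.
- **The rule does not speak of worsening.** Clinical concern may be late recognition of severity already present at T1, in which case the completer bias reverses. This stands, so the direction is likely rather than certain. The ethics section does expect nurses to notice adolescents faring worse.
- **Comparison with d = 0.3.** A reader might divide 0.20 SD by 0.3 and conclude that two-thirds of the target effect could be spurious. That is not supported: 0.3 is the target in the power calculation for daily diaries, not for the questionnaires, and 0.20 SD needs all expected dropout to be exactly the worst outcomes.
- **Deterioration is not hidden altogether.** Diaries up to discontinuation, individual-level analyses and weekly team review of monitoring data remain. This stands; what is lost is the T2 questionnaire.

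A nurse could also mark a discontinued case as completed, which would release T2. Nothing in the article tells her to, and leaving that to chance adds inconsistency.

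**Conclusion.** The point holds for T2. The two stated rules together mean that adolescents discontinued for clinical concern have no T2 in a comparison with no untreated group, and no analysis is named for the case where that loss is informative. If the loss follows deterioration, the bias is towards benefit: about 0.03–0.11 SD in completers and 0.05–0.20 SD after imputation from T1 alone. These figures rest on assumptions the article neither gives nor excludes: zero true change, correlation 0.6 and 5–15% lost for deterioration. They are an illustration, not an estimate. The bias is smaller if pre-discontinuation diaries inform the imputation, and opposite in completers if the concern reflects severity at T1. Whether T3, T4 and the diaries are affected cannot be determined from the article. The change is worth making because it is cheap and the sample is small.

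**What to change.** Leave the rule on discontinuation and referral as it is, and change only what happens to the data:

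1. Trigger T2 when Kort ends for any reason, including referral, and record the reason.
2. State that T3 and T4, and diaries if the adolescent agrees, continue after Kort ends.
3. Include diary data from before discontinuation in the imputation model for the questionnaire outcomes.
4. Report the number discontinued for clinical concern beside the mean change.
5. Add one sensitivity analysis that applies an unfavourable shift, for example 0.5 and 1 SD, to the imputed values of those whose later data are missing.

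The cost is a few more automated questionnaires, optional for the adolescent, one added reason field in the nurse's form, and one extra analysis. The estimated change may look smaller.
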